#### Participant timeline {13}

Figure 1 show the recommended SPIRIT figure with the participant timeline.

**Fig. 1 Fig1:**
[figure not shown]
The recommended SPIRIT figure with the participant timeline

#### Sample size {14}

To determine the number of volunteers, the sample size was calculated using the GPower software version 3.1, for a 95% confidence level and 80% study power. The calculation was based on a pilot study (unpublished) that considered the LF/HF index of HRV, and systolic blood pressure. The largest suggested sample size was 19 volunteers per group to detect a decrease in systolic blood pressure with an effect size of 0.80. Therefore, considering possible dropouts, 25 participants will be enrolled for each group.

#### Recruitment {15}

Participants will be recruited from the community by radio and online advertisements and notices, advertisements posted in strategic places such as neurological clinics. Also, researchers will contact the director of all Public Family Health Center (CESFAM) in the region of Maule to present the project and to check for potential participants. If a participant has no confirmed diagnosis of Parkinson’s disease, he/she will be referred to a board-certified neurologist who will apply the UK Brain Bank criteria [24].

### Assignment of interventions: allocation

#### Sequence generation {16a}

A researcher not involved in this study will be in charge to generate the sequence number using a computerized algorithm (https://www.graphpad.com/quickcalcs/randomize2/). Participants will be randomly assigned, in a 1:1 ratio, to one of the two groups studied (1) exercise (coded as “A”) or (2) AMPS + exercise (coded as “B”).

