## Methods: participants, interventions, and outcomes

### Study setting {9}

The study will be carried out at the Laboratory of Clinical Research in Kinesiology from the Universidad Católica del Maule, Talca, Maule, Chile and Human Movement Research Laboratory (MOVI-LAB), Bauru, Brazil.

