#### Concealment mechanism {16b}

After the sequence number is generated, opaque sealed envelopes containing the letters “A” or “B” will be prepared according to the predefined sequence. The envelopes will be kept safe by the same researcher in charge of sequence generation.

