#### Implementation {16c}

Sequence number is generated by a researcher blinded to the study protocol. Opaque envelopes in numerical order will is then prepared and kept in a safe place until baseline assessments are concluded. Participants are recruited in the community, where the study takes place, by all researchers involved. Participants meeting the inclusion criteria proceed to the baseline assessments. Then, prior the beginning of the intervention the envelope labeled with the same number as assigned to the participants when they were included in the study will be unsealed and informed to the leading research. Figure 2 shows the study design flowchart describing all the steps of the study (Fig. 2).

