### Data collection and management

#### Plans for assessment and collection of outcomes {18a}

Both interventions (AMPS and exercise) will be carried out within the facilities of the Catholic University of Maule, located at [name], in the city of Talca, in parallel with Human Movement Research Laboratory of the São Paulo State University, Brazil. Evaluations will be conducted in a room with temperature maintained between 22 and 24 °C and relative humidity between 40 and 60% at the same time of day (2:00 p.m. to 6:00 p.m.) to minimize the influences of circadian variations. The methodological procedures for obtaining each outcome are detailed below:

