### Statistical methods

#### Statistical methods for primary and secondary outcomes {20a}

The Shapiro-Wilk and Levene’s tests will be applied to check for data normality and the homogeneity of the variance, respectively. To check the interaction between the Groups (EX-G and AMPS-G) and time (baseline and post-intervention) a mixed ANOVA model with Bonferroni adjustment will be applied for the variables that meet the ANOVA assumptions. Otherwise, the data will be analyzed by the Wilcoxon (intragroup) and Mann-Whitney (intergroup) tests with a priori Bonferroni correction. For all tests, the significance level will be set at 5%.

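### Two sites in two countries, but the allocation as described has no site stratum and the stated analysis model has no site term

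*Protocol article*

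**What the plan says.** Study setting {9} names laboratories at "Talca, Maule, Chile and Human Movement Research Laboratory (MOVI-LAB), Bauru, Brazil". Plans for assessment and collection of outcomes {18a} says that both interventions run in Talca "in parallel with Human Movement Research Laboratory of the São Paulo State University, Brazil".

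Allocation is described in three short sections:
- Sequence generation {16a}: "A researcher not involved in this study will be in charge to generate the sequence number using a computerized algorithm". The ratio is 1:1 to exercise or AMPS plus exercise.
- Concealment mechanism {16b}: the envelopes "will be prepared according to the predefined sequence", and "The envelopes will be kept safe by the same researcher in charge of sequence generation".
- Implementation {16c}: after baseline, what is opened is "the envelope labeled with the same number as assigned to the participants when they were included in the study".

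None of these mentions site, strata, blocks or more than one list.

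Statistical methods {20a} tests the interaction of group and time: "a mixed ANOVA model with Bonferroni adjustment will be applied for the variables that meet the ANOVA assumptions". Otherwise Wilcoxon tests are used within groups and Mann-Whitney tests between groups. Section {20b} plans no additional analyses. Sample size {14} sets enrolment at 25 per group.

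**The concern.** Two laboratories in different countries can differ in how participants respond over 12 weeks: who delivers the stimulation and the exercise, the usual physiotherapy that participants may keep, and the population recruited. The article gives some reason to expect this. The cognitive screen is adjusted for the Chilean and the Brazilian population, and health-centre recruitment is described only for the Maule region.

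If allocation is not balanced within site, chance can put noticeably more of one arm at one site when there are only 50 participants. If site is also missing from the analysis, a difference between sites in change is either carried into the arm contrast, when the split is uneven, or left in the error term, when it is even. At stake are the precision of the comparison and how readily an observed difference can be attributed to AMPS in a small trial.

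**Working it through.** **Inputs from the article.** Two sites; 1:1 allocation; 25 per group enrolled, 50 in all; standardized effect 0.80; 5% significance; 80% power; 19 per group before dropouts.

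**Assumptions, because the article gives no figures.** Arm totals fixed at 25:25; m participants at one site, with m from 10 to 25; site difference D in the analysed change, in within-site SDs, from 0 to 1.0; all 50 analysed.

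**The plan's own figure.** n per group = 2(z_alpha + z_beta)²/d². One-sided: 2(1.645 + 0.842)²/0.64 = 19.3, close to the stated 19 (20 when rounded up; 21 by the exact t-test). Two-sided: 2(1.960 + 0.842)²/0.64 = 24.5, so 25 (26 by the exact t-test). The article does not state the sidedness. The power figures below are two-sided at the enrolled 25 per arm, where the t-test gives 79.2% for d = 0.80.

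**Step 1: chance of imbalance.** With X the number in the AMPS arm at a site of m, X is hypergeometric (50 in total, 25 in AMPS, m drawn). The gap between arms in site share is |2X − m|/25.

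| m at one site | Split or worse | Gap in site share | Probability |
|---|---|---|---|
| 25 | 15:10 | 5/25 = 20 points | 25.8% |
| 25 | 16:9 | 7/25 = 28 points | 8.9% |
| 20 | 13:7 | 6/25 = 24 points | 14.8% |
| 15 | 10:5 | 5/25 = 20 points | 21.7% |
| 10 | 8:2 | 6/25 = 24 points | 7.4% |

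These count both directions. The probabilities do not fall smoothly with m because only odd gaps are possible when m is odd and only even ones when m is even.

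**Step 2: effect of an imbalance on the contrast.** Shift = gap × D. For 16:9 and D = 0.5: (16/25 − 9/25) × 0.5 = 0.14 SD. For 15:10: 0.20 × 0.5 = 0.10 SD.

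**Step 3: which site differences matter.** The test is of group by time with two time points, which is a comparison of change. A difference between sites that is the same at baseline and at 12 weeks subtracts out. Only a difference in change remains. The Mann-Whitney fallback is not said to use change; if it is applied to post-intervention values, level differences enter as well.

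**Step 4: power without a site term.** With s the share of participants at one site, the SD of change over both sites is √(1 + s(1 − s)D²) and the effective effect is 0.80 divided by that. The simulated figures are for a 50:50 site split with 40,000 runs.

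| D | SD, 50:50 | Effective d | Power, 50:50 | Power, 20:80 | Simulated, no site term | Simulated, site term |
|---|---|---|---|---|---|---|
| 0 | 1.000 | 0.800 | 79.2% | 79.2% | 79.0% | 78.2% |
| 0.5 | 1.031 | 0.776 | 76.7% | 77.6% | 76.4% | 78.1% |
| 1.0 | 1.118 | 0.716 | 69.8% | 73.0% | 69.7% | 78.1% |

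Simulated type I error was between 4.8% and 5.0% in every case, with or without the site term.

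**The case against.** The strongest reply is that much of this rests on silence. No sentence says the sequence is unstratified. That reading comes from singular wording, one numbered series, one custodian and no mention of strata. A journal article condenses a fuller protocol, and block and stratum details often sit there. This stands, and it is why the allocation half of the point is secondary. It carries less weight for the analysis, where the article states the factors and the fallback outright and site is in neither.

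Two stronger readings are tempting, and the documents support neither:
- A reader might infer that site is confounded with treatment. Randomization leaves only chance imbalance, the estimate is unbiased over repetitions, and type I error holds at about 5% without a site term. Constant level differences between assessors, devices or populations also cancel in the planned interaction test.
- A reader might infer that one envelope series cannot serve two countries and must be split ad hoc. The article ties each envelope to an inclusion number, leaves custody with one outside researcher and has the result passed to the lead researcher. Central opening with remote release fits that description.

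The size is also open to challenge. The 0.14 SD shift needs an even site split, a 9% event and a 0.5 SD site difference in change, all against a design effect of 0.80. The article gives one procedure and one set of room conditions for both sites and reports no site difference. This stands as a limit on magnitude: at D = 0.5 the power loss is under 3 points.

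**Conclusion.** The point holds as one of precision and chance balance. As described, allocation is not stratified by site, and the stated model and its fallback ignore site. Imbalance of 20 points or more in site share has a chance of 7% to 26% across the site splits examined. The power cost is small for a modest site difference in change (79% to about 77% at 0.5 SD) and material for a large one (70% at 1.0 SD). A site term costs about 1 point if sites do not differ and holds power at about 78% if they do.

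The site split and the site difference are assumptions, and attrition would change the figures. The change is worth making because it is nearly free. Leaving it out would not invalidate the trial.

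**What to change.** **Main change, in Statistical methods {20a}.** Add site as a fixed factor to the primary model for all participants, and specify that it acts on change: include site by time in the mixed ANOVA, or equivalently site in an analysis of change. A site main effect on level alone would not remove a site difference in change. For the fallback, name a site-stratified rank test on change scores, such as the van Elteren test. The cost is one degree of freedom. It should be fixed before unblinding. If a full analysis plan already contains this, one sentence in {20a} is enough.

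**Optional change, in Sequence generation {16a} to Implementation {16c}.** Recruitment is stated to run to October 31, 2022. For participants not yet randomized, the independent researcher could prepare a separate list per site, with randomly varying block sizes that are not disclosed and with envelopes still held and opened by that researcher after baseline. The costs are a new list and envelope set, and slightly greater predictability for the unblinded lead, since all researchers take part in recruitment. Exact 25:25 totals may also be lost when lists change partway. If site lists already exist, saying so settles this part.

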#### Concealment mechanism {16b}

After the sequence number is generated, opaque sealed envelopes containing the letters “A” or “B” will be prepared according to the predefined sequence. The envelopes will be kept safe by the same researcher in charge of sequence generation.

#### Implementation {16c}

Sequence number is generated by a researcher blinded to the study protocol. Opaque envelopes in numerical order will is then prepared and kept in a safe place until baseline assessments are concluded. Participants are recruited in the community, where the study takes place, by all researchers involved. Participants meeting the inclusion criteria proceed to the baseline assessments. Then, prior the beginning of the intervention the envelope labeled with the same number as assigned to the participants when they were included in the study will be unsealed and informed to the leading research. Figure 2 shows the study design flowchart describing all the steps of the study (Fig. 2).

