### Who will take informed consent? {26a}

[name] researcher will be in charge to contact potential participants via telephone and invite them to participate in the study. In case we have a positive reply, an appointment will be scheduled and [name] will explain the objectives of the study, the inclusion and exclusion criteria, participant’s roles, risks, benefits, and ethical implications. If the participants agree in took part in the study, they will be requested to sign two copies of an informed consent, one for the participants and the other for the researcher.

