### Assignment of interventions: blinding

#### Who will be blinded {17a}

This will be a double-blinded study. Participants will be assigned to exercise plus AMPS or Exercise plus SHAM group. Thus, participants will be not aware if they are assigned to active AMPS or sham. Also, the researchers responsible for outcome assessments, data entry, and statistical analysis will be blinded to the group assignments. The leading research who will be in charge of the AMPS therapy will not be blinded, since it is not possible.

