##### Peak oxygen uptake

All participants will undergo a cardiopulmonary exercise testing (CPET) studies in a global and non-invasive way the integral response of the organism to exercise, through a rational analysis of the respiratory, cardiovascular, hematopoietic, neuropsychological, and skeletal muscle systems [32] CPET will be performed with an ergometric bike (Ergoselect 5 M, Ergoline, Germany). An incremental ramp-type protocol will be used to determine the workload imposed on aerobic training and possible comorbidities that impede the performance of the proposed physical training protocol [33]. The outcomes VO2, carbon dioxide output (VCO_2_), ventilation (VE), and respiratory exchange ratio (RER) will be obtained on a breath-to-breath basis during the entire CPET using an expired gas measurement system (metalyzer 3b - Cortex Medical, Germany) duly calibrated before each test (this equipment is available for common use in our university). During CPET, electrocardiogram and heart rate (HR) will be continuously recorded in real-time via a 12-lead integrated ECG (Quark T12, Cosmed, Italy). Blood pressure and the ratings of perceived exertion using the Borg CR10 scale will be monitored throughout the test.

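### The unblinded lead researcher, who is told every allocation, is not barred from enrolling participants; enrolment should be separated from knowledge of past allocations

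*Protocol article*

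**What the plan says.** Implementation {16c} states that "Participants are recruited in the community, where the study takes place, by all researchers involved". It then sets the order of steps: inclusion criteria met, baseline assessments, envelope opened. The envelope used is the one matching the number given at inclusion: "the envelope labeled with the same number as assigned to the participants when they were included in the study will be unsealed". The result "will be unsealed and informed to the leading research".

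Who will be blinded {17a} adds: "The leading research who will be in charge of the AMPS therapy will not be blinded, since it is not possible".

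Three safeguards are stated. Sequence generation {16a} gives the list to a researcher outside the study. Concealment mechanism {16b} uses opaque sealed envelopes kept by that same person. Implementation {16c} holds them back until baseline is concluded.

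Who will take informed consent? {26a} gives telephone invitation and consent to one researcher, whose name is removed in the text at hand. Sample size {14} says that "25 participants will be enrolled for each group". Beyond the 1:1 ratio, the article states no restriction on the sequence.

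**The concern.** Sealed envelopes hide the next letter but not the letters already opened. The codes A and B are decoded in Sequence generation {16a}, so they mask nothing from someone who is told the allocations. If the list is balanced in some way, the running count says something about what comes next. A recruiter who holds that count and hopes AMPS works could, even without intent, choose whom to approach or when to admit them.

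The setting leaves room for this. Trial status gives recruitment from 30 July 2021 to 31 October 2022 against a 12-week intervention, so many allocations will be known while recruitment continues. Trial design {8} describes non-probability sampling, and Recruitment {15} has researchers looking for candidates through health centres, so the choice and timing of invitations are discretionary. Selection bias of this kind cannot be removed in the analysis and is hard to see in baseline tables of 50 people.

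**Working it through.** **Inputs.** From the documents: 1:1 allocation {16a}, 25 per group {14}, all researchers recruit {16c}, lead researcher told each allocation {16c} and unblinded {17a}. Assumed: the list design, the number of envelopes unopened at any time, and the number lost before opening. The plan gives no figure on predictability, so there is none to reproduce.

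**Step 1: how well the next arm can be guessed when every earlier allocation is known.** The guesser names the arm with more places left and tosses a coin when they are equal. For a balanced block of N, the expected number of correct guesses is N/2 + 2^(N−1)/C(N, N/2) − 1/2.

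| Assumed list | Calculation | Share correct |
|---|---|---|
| Simple randomisation | no information in the past | 50% |
| One list, 25 + 25 | 25 + 4.453 − 0.5 = 28.95 of 50 | 57.9% |
| Blocks of 10 | 5 + 512/252 − 0.5 = 6.53 of 10 | 65.3% |
| Blocks of 6 | 3 + 32/20 − 0.5 = 4.10 of 6 | 68.3% |
| Blocks of 4 | 2 + 8/6 − 0.5 = 2.83 of 4 | 70.8% |

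Simulation of the 25 + 25 list gives the same 57.9%, and about 70% for the last ten places.

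**Step 2: allow for unopened envelopes.** Numbers are given at inclusion and envelopes opened only after baseline, so participants still in baseline leave gaps in the count. For the 25 + 25 list (40,000 simulated lists):

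| Numbered but unopened (assumed) | All 50 | Last ten |
|---|---|---|
| 0 | 57.9% | about 70% |
| 4 | 55.6% | about 62% |
| 8 | about 54% | about 60% |

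For blocks of four the four positions can be written out. With no gap: 1/2 + 2/3 + 2/3 + 1 = 2.83 of 4, or 70.8%. With one unopened: 1/2 + 1/2 + 2/3 + 2/3 = 2.33, or 58.3%. With two: 1/2 + 1/2 + 1/2 + 2/3 = 2.17, or 54.2%. With three or more: 50%. The Step 1 figures are therefore upper limits for each design.

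**Step 3: envelopes never opened.** Peak oxygen uptake says baseline exercise testing may reveal "possible comorbidities that impede the performance of the proposed physical training protocol", so some numbered participants may leave before their envelope is opened. Suppose a 25 + 25 list with 5 or 10 such losses and no replacement. The SD of one arm's count is √(45 × 0.25 × 5/49) = 1.07 or √(40 × 0.25 × 10/49) = 1.43, and the mean difference between arms is 1.8 or 2.2 people. Power at the protocol's effect size of 0.80 (two-sided 5% t-test) is 74.5% or 69.1%, against 74.6% or 69.3% for equal arms of the same total. The imbalance costs at most about 0.2 percentage points; the rest of any loss comes from having fewer participants.

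**The case against.** The strongest reply is that concealment is properly described. The list-maker is outside the study, the envelopes are opaque and sealed, the same outsider keeps them, and they are released only after baseline. A reader might infer that recruitment can simply be steered, but past letters reveal nothing under simple randomisation and rarely give certainty otherwise. This stands, and it limits the point to an avoidable exposure.

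Four other strong readings are also not supported:

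- **One list ending at 25 per arm.** Sample size {14} gives an enrolment target, not a list structure. Two sites run in parallel, and the number of lists is not stated. An article may leave that to the full protocol.
- **Early numbering breaks concealment.** The envelope stays closed, and a number fixed at inclusion prevents later reordering. It would matter only to someone who could predict the letters, and the article does not say who gives out numbers.
- **Unused envelopes break the 1:1 ratio or exhaust the list.** No loss count, list length or replacement rule is stated, the point in baseline at which someone counts as included is not defined, and the flowchart is not shown. At the assumed losses the result is slight random imbalance, not bias.
- **The consent and recruitment sections contradict each other.** Under {26a} one "researcher will be in charge to contact potential participants via telephone and invite them to participate in the study", while everyone else may publicise the trial as Recruitment {15} describes. The two can be read together. Because the name is removed, nobody can tell from this text whether the consenting researcher is the lead researcher.

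What the reply does not remove is that no sentence keeps the one person told every allocation out of enrolment.

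**Conclusion.** The point holds as a matter of role separation. The article lets a person who knows past allocations take part in choosing and admitting participants. The gain in guessing the next arm runs from nothing (50%, simple randomisation) to at most about 58% (one 25 + 25 list) or about 71% (blocks of four), and is lower when envelopes are pending. Every figure above 50% rests on an assumed list design. The documents show neither that steering would occur nor that concealment has failed. The case for acting is that separating the roles removes the exposure whichever list was used. Unused envelopes are a minor operational matter.

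**What to change.** In Implementation {16c}:

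1. State that the lead researcher and any other AMPS or sham operator, at either site, take no part in inviting participants, deciding eligibility, taking consent or giving out numbers. State that allocations are disclosed only to the operator and are not shared at the two-weekly meetings of all researchers.
2. As a secondary change, keep the study ID separate from the randomisation number. The independent holder opens the next envelope in order only once baseline is complete and eligibility confirmed. This avoids unused envelopes. Make this change together with the first: opening in strict order after baseline shortens the gap in Step 2, so on its own it would leave an unblinded recruiter with a more current count.

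The cost is a few lines of protocol text and a change of duties among existing staff, submitted to the ethics committee as an amendment. The lead researcher can no longer help with enrolment. Recruitment was already open when this version was dated, so the change would protect those not yet enrolled.
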